## Abstract

**Introduction:**

Patients with chronic kidney disease (CKD) display increased infection-related mortality and elevated cardiovascular risk only partly attributed to traditional risk factors. Patients with CKD also exhibit a pro-inflammatory environment and impaired immune function. Aerobic exercise has the potential to positively impact these detriments, but is under-researched in this patient population. This feasibility study will investigate the effects of acute aerobic exercise on inflammation and immune function in patients with CKD to inform the design of larger studies intended to ultimately influence current exercise recommendations.

**Methods and analysis:**

Patients with CKD, including renal transplant recipients, will visit the laboratory on two occasions, both preceded by appropriate exercise, alcohol and caffeine restrictions. On visit 1, baseline assessments will be completed, comprising anthropometrics, body composition, cardiovascular function and fatigue and leisure time exercise questionnaires. Participants will then undertake an incremental shuttle walk test to estimate predicted peak O_2_ consumption (VO_2_peak). On visit 2, participants will complete a 20 min shuttle walk at a constant speed to achieve 85% estimated VO_2_peak. Blood and saliva samples will be taken before, immediately after and 1 hour after this exercise bout. Muscle O_2_ saturation will be monitored throughout exercise and recovery. Age and sex-matched non-CKD ‘healthy control’ participants will complete an identical protocol. Blood and saliva samples will be analysed for markers of inflammation and immune function, using cytometric bead array and flow cytometry techniques. Appropriate statistical tests will be used to analyse the data.

**Ethics and dissemination:**

A favourable opinion was granted by the East Midlands-Derby Research Ethics Committee on 18 September 2015 (ref 15/EM/0391), and the study was approved and sponsored by University Hospitals of Leicester Research and Innovation (ref 11444). The study was registered with ISRCTN (ref 38935454). The results will be presented at relevant conferences, and it is anticipated that the reports will be published in appropriate journals in 2018.

Strengths and limitations of this studyInclusion of control group matched for age and sex.A variety of outcome measures to inform future study design.Pragmatic study design which will inform future exercise recommendations for patients with CKD.No non-exercise control visit.

## Introduction

Patients with all stages of chronic kidney disease (CKD) have elevated cardiovascular disease (CVD) risk that cannot be fully explained by traditional risk factors.^1^ CVD is the most common cause of death among patients with CKD (23% in 2013), followed by infection (19% in 2013).^2^

Patients with CKD are often sarcopenic and obese,^3–6^ and further deterioration in these characteristics is often observed after renal transplantation.^7–9^ Patients with CKD and renal transplant recipients (RTRs) also frequently suffer from chronic systemic inflammation,^10 11^ which can worsen cachexia and increase cardiovascular risk in CKD.^12 13^ Patients with CKD and RTRs also display impaired cellular immune function,^14–16^ which may explain why infection is the second-leading cause of death in this population.^2^ This effect (ie, impaired immune function) is further compounded in RTRs by the immunosuppressive drug regime. Impaired immune function may further exacerbate inflammation due to alterations in circulating immune cell subsets^17^ which could serve to worsen body composition and increase cardiovascular risk. Finally, patients with CKD display elevated levels of circulating prothrombotic microparticles (MPs),^18^ which may worsen CVD risk and/or burden.^19^

Exercise has the potential to benefit and improve many of the aforementioned inter-related morbidities. In the general population, exercise can positively impact on weight gain,^20^ muscle wasting,^21^ physical capacity^22^ and fatigue.^23^ Furthermore, moderate aerobic exercise can also modify systemic inflammation,^24 25^ bolster immune function via alterations in circulating immune cell populations and activity and reduce circulating MP levels.^26–29^

In the CKD population, similar positive effects of exercise on body composition, physical function and quality of life have been demonstrated^30–33^; however, the research on inflammation and immune function in this population is limited. Previous research has shown that 30 min of moderate intensity walking exercise elicited a normal pattern of leucocyte and monocyte activation, while enhancing granulocyte function and promoting an anti-inflammatory environment (increased IL-10 release) in patients with pre-dialysis CKD.^34^ However, in a similar population, an exhaustive bout of cycling exercise elicited a shift towards the more proinflammatory CD16^+^ monocyte, potentially favouring inflammation.^35^ This disparity may be due to the exercise intensities investigated—moderate intensity exercise is more beneficial in strengthening immune function and preventing infection^26^ and is promoted in general exercise guidelines. As such, investigating the effects of moderate intensity exercise in this patient population is more pragmatic and will help to guide future exercise recommendations, which are lacking in this patient population.

Therefore, this feasibility study aims to investigate the effects of acute aerobic walking exercise on the inflammation and immune function in patients with CKD. This will create the basis from which a larger trial can be conducted, including data for a power calculation, which will ultimately help to inform exercise recommendations in this population which are currently lacking, particularly with regards to immune function and inflammation.^36^ However, a preliminary power calculation (GPower V.3.1) based on the findings of Viana *et al*^34^ concerning total lymphocyte count (based on a statistical power of 0.80 and an alpha level of 0.05) suggests that 15 participants per group (eg, predialysis CKD, RTRs and healthy controls) will be sufficient.

## Methods and analysis

### Outcomes to be measured

This study will investigate the effect of 20 min of moderate intensity walking exercise on immune cell subsets and inflammatory markers. Participants will be grouped based on their status (ie, ‘patient’ or ‘healthy control’). Both groups will complete an identical acute, cross-sectional study protocol necessitating two study visits, as explained below.

### Participant recruitment

All patients with CKD attending outpatient clinics within the University Hospitals of Leicester renal network will be screened for eligibility by their consultant nephrologist prior to recruitment, and approached during their routine outpatient appointments. The inclusion and exclusion criteria for patients are summarised in table 1. Healthy age-matched and sex-matched controls with no known chronic disease will be recruited from the local community. Those who do not believe themselves to suffer from any significant chronic disease will be eligible to participate. The ‘broad’ inclusion and exclusion criteria allow the incorporation of several different groups (ie, patients with non-dialysis CKD, with dialysis, RTRs and healthy controls), and thus will allow comparison between these groups. Similarly, the wide range of CKD stage will allow the influence of remaining renal function on the measured markers to be investigated.

**Table 1 T1:** Inclusion and exclusion criteria for patients

Inclusion criteria	Exclusion criteria
Established chronic kidney disease (all stages will be eligible including those with an established kidney transplant and those receiving dialysis treatment)	Age under 18 years Pregnancy Received kidney transplant less than 6 months prior to study entry Any element of study assessment protocol considered by principle care provider to be contraindicated due to physical impairment, comorbidity or any other reason Inability to give informed consent for any reason Visual or hearing impairment or insufficient command of English to give informed consent or comply with the assessment protocol

### Trial design and timeline

This is a non-randomised, controlled, feasibility study. Participants will complete two study visits as described below.

### Visit 1

Participants will arrive at the laboratory in the morning, unfasted but having consumed no caffeine or alcohol and completed no strenuous exercise for 24 hours. Participants will complete questionnaires about time spent in leisure activity and their perception of fatigue, and assessments of anthropometry, body composition and cardiovascular condition. Participants will then undertake the Incremental Shuttle Walk Test (ISWT), followed by the Endurance Shuttle Walk Test (ESWT) as explained below. If the participant cannot complete the full 20 min duration of the ESWT, they will be withdrawn from the study.

### Visit 2

Participants will arrive at the laboratory in the morning (8–10 am, to minimise the influence of diurnal variation on immune parameters), following the same standardisation procedure as in visit 1. After resting for 10 min, blood and saliva samples will be collected. The ESWT will then be completed at the same speed as in visit 1, lasting for 20 min. Within 5 min of exercise cessation, another blood and saliva sample will be collected. The participant will then rest for 1 hour, after which a final blood and saliva samples will be collected. This protocol is summarised in a schematic in figure 1, and the outcome measures are explained in greater detail below.

**Figure 1 F1:**
[figure not shown]
Visit 2 exercise and sample collection protocol. ↓, venous blood and saliva collection. ESWT, Endurance Shuttle Walk Test.

The time delay between recruitment, visit 1and visit 2 will be kept to a minimum to prevent deconditioning and minimise dropout rates. For dialysis patients, both study visits will be completed on a non-dialysis day that is not after their ‘long break’ (ie, weekend or two consecutive days without dialysis based on their regular shift pattern) to minimise the effect of fluid overload.

### Physical performance

Endurance capacity will be assessed using the ISWT^37^ and ESWT.^38^ In the ISWT, the participant walks a level 10 m shuttle course at a speed controlled by an external audible bleep signal. The test progressively increases at 1 min interval for a total of 12 intervals and is terminated when the participant fails to complete a shuttle within the required time. Following the ISWT, a walking speed equating to 85% of predicted peak O_2_ consumption (VO_2_ peak) can be calculated, using a conversion table based on their ISWT performance. The ESWT is completed at this continuous speed on the same shuttle course until volitional exhaustion or the end of the test (20 min) is reached. For the purposes of this study, any participant who does not complete the full 20 min of the ESWT in visit one will be excluded to ensure standardisation of the test in visit 2. This protocol was initially developed for use in patients with chronic airways obstruction^37^ but has been used in the CKD population,^39 40^ showing good reproducibility and a high correlation with VO_2_peak.^41^

### Venous blood sampling

Venous blood will be collected using venepuncture of the antecubital vein of either arm—provided the absence of an arteriovenous fistula. Blood will be drawn through a 21- gauge needle (30 mL per time point) and collected into di-potassium EDTA, sodium citrate, sodium heparin and blank monovettes.

### Blood processing, storage and analysis

Blood collected into EDTA tubes will be centrifuged at 4°C; the supernatant will then be aliquoted and frozen at −80°C for future analysis. A cytometric bead array technique will be used to allow bulk analysis of a panel of proinflammatory and anti-inflammatory cytokines, including but not limited to IL-1, IL-2, IL-6, IL-10, tumour necrosis factor alpha and interferon gamma. Blood collected into sodium citrate^42^ will be double centrifuged at room temperature (15 min at 2500 *g*, supernatant aliquoted followed by another 15 min at 2500 *g*) to create platelet-poor plasma; the supernatant will then be aliquoted and frozen at −80°C for future phenotyping of microparticles using flow cytometry, as explained below. Blood collected into sodium heparin will be analysed on the day of collection for immune cell subsets using flow cytometry, as explained below. Blood collected into blank monovettes will be sent to the Diagnostic Pathology Service at University Hospitals of Leicester National Health Service (NHS) Trust on the day of collection for renal profile analysis, which includes estimated glomerular filtration rate, urea, bicarbonate, creatine, sodium, potassium and phosphate measures. This will be completed for both patient and control populations.

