### Data analysis plan

Mixed-design analyses of variance will be used to analyse main effects of group and time and interaction effects, with Bonferroni post hoc testing used to elucidate these effects. This will generate both tests of significance and estimates of effect sizes. Any non-normally distributed data will first be transformed appropriately to ensure normality assumptions are met, to increase statistical power and to allow clear conclusions to be drawn from the data. Where normality assumptions cannot be met via data transformation, Friedman’s tests will be employed as a non-parametric alternative. This will allow the generation of hypotheses for future, larger studies.

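### No haemoglobin or haematocrit is named at the three sampling times, so a fall in plasma volume after exercise could pass as a time effect in concentration-based plasma markers

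*Protocol article*

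**What the plan says.** Under Trial design and timeline (Visit 2), the baseline draw is described as "After resting for 10 min, blood and saliva samples will be collected". The next is described as "Within 5 min of exercise cessation, another blood and saliva sample will be collected", and a last one follows 1 hour of rest. The abstract describes the exercise between the first two: "participants will complete a 20 min shuttle walk at a constant speed to achieve 85% estimated VO_2_peak".

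Venous blood sampling lists four tube types, and Blood processing, storage and analysis gives each a use:

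- EDTA: spun cold and the plasma frozen for cytokines. The assay sentence is "A cytometric bead array technique will be used to allow bulk analysis of a panel of proinflammatory and anti-inflammatory cytokines".
- Citrate: double-spun and frozen for microparticles.
- Heparin: same-day flow cytometry of immune cells.
- Blank: sent to the hospital laboratory for "renal profile analysis, which includes estimated glomerular filtration rate, urea, bicarbonate, creatine, sodium, potassium and phosphate measures".

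The Data analysis plan then says "Mixed-design analyses of variance will be used to analyse main effects of group and time and interaction effects". Neither section mentions haemoglobin, haematocrit, total protein, a full blood count or an adjustment for plasma volume. Fluid status appears only in the scheduling of dialysis patients' visits.

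**The concern.** A concentration can rise because more of the substance has entered the plasma or because there is less plasma. The second sample is drawn within minutes of exercise, when a fall in plasma volume is plausible, and the third after an hour of rest, when some or all of it may have reversed. A marker that was never released would then rise and fall back, which is a pattern the time effect is meant to detect.

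Separating the two explanations normally needs haemoglobin and haematocrit from whole blood at each time point. As written, the EDTA blood is spun with neither measured. This is a gap in data collection, so an analysis plan written later could not properly repair it. The study is meant to provide effect sizes and a power calculation for a larger trial, so an inflated time effect could be carried into that design.

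**Working it through.** **The plan's own figure.** The Introduction's preliminary calculation "suggests that 15 participants per group", "based on a statistical power of 0.80 and an alpha level of 0.05". It concerns total lymphocyte count and gives no effect size, SD, test or correlation, so it cannot be reproduced. Solving back from n = 15 at 80% power and two-sided 0.05 gives a standardised effect of 0.78 (paired t), 1.06 (two-sample t) or f = 0.48 (one-way comparison of three groups). None of these concerns a plasma marker. Below, 15 is used only as the group size.

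**Inputs.** From the protocol: three sampling times, 15 per group, and comparisons of time and of group by time. Assumed, because the protocol gives no values: the fractional fall in plasma volume x, and the SD s of the within-person log change.

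**Step 1: apparent rise with no release.** If the circulating amount is unchanged, post/pre = 1/(1 − x), so the apparent rise is 1/(1 − x) − 1.

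- x = 0.02: 1/0.98 − 1 = 2.0%
- x = 0.05: 1/0.95 − 1 = 5.3%
- x = 0.10: 1/0.90 − 1 = 11.1%
- x = 0.15: 1/0.85 − 1 = 17.6%

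Multiplying the post-exercise value by (1 − x) returns each of these to 0%.

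**Step 2: how often an unchanged marker would be declared changed.** Paired t test on the log scale, one group of 15, two-sided 0.05, noncentrality −ln(1 − x)/s × √15. For example, x = 0.10 and s = 0.20 give 0.1054/0.20 × 3.873 = 2.04 on 14 df, a rejection rate of 48%.

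| Fall in plasma volume | s = 0.10 | s = 0.20 | s = 0.30 | s = 0.50 |
|---|---|---|---|---|
| 2% | 11% | 6.5% | 5.7% | 5.2% |
| 5% | 46% | 15% | 9.5% | 6.6% |
| 10% | 97% | 48% | 25% | 12% |
| 15% | over 99% | 83% | 50% | 22% |

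**Step 3: group by time.** Suppose one group loses 10% and another 5%. The spurious ratio of changes is 0.95/0.90 = 1.056, or 5.6%. As a difference in percentage rise it is 11.11 − 5.26 = 5.85 points. A two-sample t test on log change, 15 per group, rejects in 30%, 11%, 7.6% and 5.9% of trials at s = 0.10, 0.20, 0.30 and 0.50.

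On the untransformed scale, an equal 10% fall adds 0.11 to a baseline of 1 and 0.22 to a baseline of 2. Unequal baselines alone can therefore create an interaction; a log scale removes it.

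Steps 2 and 3 use single t tests in place of the mixed ANOVA. The planned Bonferroni step would lower these rates but leave the bias in Step 1 unchanged.

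**The case against.** The strongest objection is that this rests on silence in a condensed article. No sentence calls the values raw or uncorrected, no reporting unit is given, and the full protocol may name a blood count. That stands in part, and is why the fix allows for simple confirmation. But the article is not sparse here: it gives tube types, centrifuge settings and the contents of the renal panel, and on that account nothing supplies the two measurements.

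Size is the next objection. The plasma-volume falls and SDs are assumptions, and the plan calls the walk moderate. For highly variable cytokines the effect is slight: at s = 0.50, even a 10% fall raises the rejection rate only to 12%. This stands and limits the point.

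Third, the concentration actually circulating is a legitimate quantity in its own right. This also stands, so corrected values belong beside uncorrected ones and should not replace them.

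Four stronger readings are tempting but not supported:

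- **Patients and controls differ in haemoconcentration.** Each person's speed is set from their own shuttle-walk result, and nothing in the protocol shows a differential shift. The scheduling rule for dialysis patients is a precaution, not evidence of one.
- **The missing non-exercise visit is the cause.** A resting visit would not contain exercise-induced haemoconcentration, so the exercise-minus-rest contrast would still carry it.
- **All microparticle results are affected.** The preparation restores the sample volume with buffer, so counts would follow plasma concentration, but percentages or phenotype shares would not. The unit is not stated.
- **Nothing can be recovered later.** Total protein in the frozen EDTA plasma might serve as an imperfect index, if enough volume remains.

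**Conclusion.** The concern holds in a limited form. As written, the plan names no measurement from which to calculate plasma-volume change and states no correction, so any fall at the immediate post-exercise sample would appear as a time effect in plasma markers expressed as concentrations. Under an assumed fall of 5% to 15% the apparent rise is 5.3% to 17.6% with no release.

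Whether this misleads depends on the marker. With 15 participants and a 10% fall, the false-positive rate runs from 97% at s = 0.10 to 12% at s = 0.50, so the problem lies mainly with low-variability markers or large falls. The group-by-time artefact is secondary: at falls of 10% against 5% it gives about 6% to 8% rejection for s between 0.30 and 0.50, close to the nominal 5%. All of these sizes rest on assumed values. What the protocol itself shows is the missing measurement and the direction of the bias if plasma volume falls.

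**What to change.** State whether haemoglobin and haematocrit are already measured at each of the three time points. If not, take both from the EDTA blood already drawn, before it is centrifuged, and calculate each participant's percentage change in plasma volume from the pre-exercise sample.

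Add to the analysis plan that cytokine and microparticle concentrations will be reported uncorrected and corrected for plasma-volume change, side by side, and state the unit used for microparticles. For participants sampled without these values, say so and do not attribute small immediate post-exercise rises to release caused by exercise.

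No extra venepuncture is needed, and the hospital laboratory already receives same-day samples. The cost is a small assay charge per time point and a sentence or two in the plan. Some apparent rises may shrink after correction.

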### Flow cytometry

Immune cells will be characterised based on their expression of surface antigens using flow cytometry. Monocyte subsets will be categorised as classical (CD14^++^CD16^-^), intermediate (CD14^++^CD16^+^) and non-classical (CD14^+^CD16^++^).^43^ Monocyte angiotensin-converting enzyme expression will be assessed using CD143, with immunoglobulin G1 as a negative control. T cells will be categorised as helper (CD3^+^CD4^+^) cytotoxic (CD3^+^CD8^+^) and regulatory (CD4^+^CD25^+^CD127^-^) T cells. B Cells will be identified as CD3^+^CD19^+^ and NK Cells as CD3-CD56^+^. Following appropriate staining and washing procedures, immune cells will be analysed on an FACSCalibur (BD Biosciences, Oxford, UK). Acquisition templates and preliminary flow cytometry results are displayed in figure 2.

**Figure 2 F2:**
[figure not shown]
Demonstration of the gating strategy used to identify immune cell subsets. (A) Total monocyte gating. (B) Monocyte subsets (R3 = classical (CD14++CD16-), R4 = intermediate (CD14++CD16+), R5 = non-classical (CD14+CD16++) (R1 and R2 were used as preliminary gating to remove neutrophils). (C) Total lymphocyte gating. (D) Gating CD8+ cytotoxic T lymphocytes in the upper right quadrant. (E) Gating CD4+ helper T lymphocytes in the upper right quadrant. (F) Gating B lymphocytes (CD3-CD19+) in the upper left quadrant. (G) Initial T-Reg gating, identifying CD4+ lymphocytes. (H) Secondary T-reg gating, back-gated onto plot G, further identifying the CD4+ lymphocytes that are CD25+CD127-. Not all graphs display 100% of acquired cells—this has been altered independently to allow ease of gating.

Microparticles will be characterised based on their size, Annexin-v expression, cellular derivation and prothrombotic potential. Cellular derivations will be categorised as platelet derived (CD42b^+^), neutrophil derived (CD66b^+^), monocyte derived (CD14^+^) and endothelial cell derived (CD144^+^). Prothrombotic potential will be estimated using Tissue Factor (CD142^+^) expression. Following the thawing of platelet-free plasma at room temperature, samples will be double centrifuged at room temperature (30 min at 18 000 *g*, supernatant removed, discarded and replaced with an equal volume of buffer, followed by another 30 min at 18 000 *g*). Samples will then undergo appropriate staining procedures with the antibodies listed above, after which microparticles will be analysed on a BD Accuri C6 (BD Biosciences, Oxford, UK) flow cytometer. Acquisition templates and preliminary microparticle results are displayed in figure 3. The protocol for isolating and analysing MPs is based on a number of publications^42 44 45^ and in our experience produces reliable results (figure 3).

